### Primary outcomes

#### Maximum muscular strength

Both maximum knee extension and elbow flexion strengths will be evaluated under the same isometric conditions. For the knee extension test, participants will be seated in a chair specifically designed for the measurement of isometric knee extension strength (ES-1295254) equipped with a force transducer (Musclelab, Ergotest, Norway), maintaining both a hip and knee angle at 90 degrees. Participants will be directed to exert maximum strength against a pad above their ankle joint. For the elbow flexion test, participants will stand upright, holding a bar with both hands in a supine position, with the elbow at a 90-degree angle. Participants will be directed to exert maximal strength against the bar.

Following a previous protocol, participants will sustain exertion for 2–3 s during both assessments.^13^ The software (Musclelab, Ergotest, Norway) will quantify the maximum voluntary isometric contraction and the rate of force development. Each participant will complete three trials for each assessment, and the best one will be used.

#### Handgrip strength test

Handgrip strength (HG) test will be measured standing with the arms at the sides. The participants will perform one repetition in each hand to familiarise themselves with the device and the test. Each participant will be asked to squeeze the grip with maximal strength with both hands for 3 s. The highest peak strength (kg) recorded between the three attempts will be considered for analysis. A digital grip strength dynamometer will be used for this (TKK 5401; Takei Scientific Instruments, Tokyo, Japan). This measure has been associated with frailty in older people.^13 14^

#### Cardiorespiratory fitness

The 400 m walking examination is deemed a suitable and reliable test for approximating cardiorespiratory fitness (CRF).^14^ So CRF will be evaluated by measuring the time needed to complete 10 laps as rapidly as feasible on a 20 m long track. Participants will be directed to walk at their maximum pace, refraining from running.^14^ The maximum and average HR during the test will be evaluated, and the HR with the test will be finished. Also, the HR 2 min after the test will be recorded as the CRF recovery variable. A single attempt at the test will be done.

#### Postural stability

A force platform will assess postural stability during quiet standing (Musclelab, Ergotest, Norway). The short physical performance battery (SPPB) balance protocol will be followed.^15^ Participants will be maintaining a stationary stance for 30 s with arms at their sides, repeated three times in each foot position, following this order: (1) feet together with eyes open; (2) semi-tandem stance (one foot’s ankle behind the joint of the other foot) with eyes open; and (3) tandem stance (one foot’s ankle directly behind and touching the other foot’s ankle) with eyes open. Measurements such as the total centre of pressure displacement, anteroposterior and mediolateral amplitudes of the centre of pressure and the area of the centre of pressure displacement will be obtained from analyses conducted with Musclelab software (Musclelab, Ergotest, Norway).

#### Dynamic balance

The Timed Up and Go (TUG) test will assess the dynamic balance. During the TUG, participants will stand up from a chair, walk 3 m, turn around and sit back down in the chair while timed (38). Two attempts will be made, and the final value will be the best.

#### Body composition

An accredited anthropometrist will measure kinanthropometric parameters related to height and body mass according to the guidelines of the International Society for the Advancement of Kinanthropometry.^16^ The portable Leicester HR 001 stadiometer (Tanita, Illinois, USA) will be used to measure the height (cm) with a precision of 1 mL, while body mass (kg) will be assessed in light clothing and barefoot using a Tanita BC-545N electronic scale (Tanita, Illinois, USA) with a precision of 0.1 kg. Each measurement will be taken twice. If both measurements have a difference of less than 1%, their average will be calculated. Conversely, if the difference exceeds 1%, a third measurement will be taken, and the median will be considered.

Body composition will be evaluated using dual-energy X-ray absorptiometry (DEXA) through a Hologic QDR 4500A densitometer (Hologic, Massachusetts, USA). A whole-body scan will be conducted to assess lean and fat mass percentages.

Additionally, a second scan of the right proximal femur (femoral neck, trochanter region and ward area) will be performed to evaluate bone mineral density levels, osteoporosis risk and WHO-FRAX. The same certified technician will conduct all measurements and densitometry analyses following key guidelines.^17^ Participants will be evaluated in a supine position with hips in internal rotation and feet in adduction to enhance femoral neck visibility. All participants will be instructed to use the restroom before the test and wear light clothing without metallic objects or shoes.^17^ A single attempt at the test will be done.

#### Functional performance

Functional performance will be measured by 10 m of gait speed, the TUG and the SPPB.^18^

Gait speed will be assessed using a 10-metre test. Participants will be asked to walk at maximum speed without running, and the total time taken to cover the 10 m distance will be measured with two photocells (Witty, Microgate, Bolzano, Italy). The test will be performed twice, and the best one will be used.

The SPPB encompasses the postural stability assessment, five-time chair stand test and 4 m gait walk.^18^ The five times sit-to-stand test will evaluate the gauges and the duration the subject takes to transition five times from a seated posture to a standing posture with utmost speed, refraining from using their arms. The test will be performed twice, and the best one will be used. In the 4 m gait walk, participants will be asked to walk at maximum speed without running and the total time taken to cover the 4 m distance.^18^ To ensure a dependable measurement, it will be measured by two photocells (Witty, Microgate, Bolzano, Italy). The test was performed twice, and the best one was used.

Of the tests included in the SPPB, each test allowed for a potential accumulation of up to four points, yielding a score spectrum of 0– 12 points.^15^

#### Sarcopenia

The HG and chair stand tests will assess muscle strength (muscle quality). Muscle quantity will be measured through appendicular skeletal muscle mass with DEXA values, and functional performance will be measured by 4 m gait speed, TUG and the SPPB battery. The risk associated with each variable will be defined in connection with the EWGSOP2 (European Working Group on Sarcopenia in Older People) sarcopenia cut-off point.^18 19^

### Secondary outcomes

#### Demographic survey

Participants will be asked about their basic socio-demographic data at the baseline. They will also be asked about their daily physical activity level, number of falls and weight loss in the last year and information regarding their health status, such as medication and pathologies.

#### Health-related quality of life

The 36-item Short-Form Health Survey (SF-36) will be employed to assess health-related quality of life. The SF-36 evaluates physical and mental health domains across eight concepts: physical functioning, physical role functioning, bodily pain, general health perceptions, vitality, social role functioning, mental health and emotional role functioning. The validated Spanish version^20^ will be used in this study. A higher score indicates a better quality of life.^20^

#### Satisfaction with life

The Satisfaction with Life Scale questionnaire will be used to assess life satisfaction, specifically in its Spanish version.^21^ This instrument consists of five items responded to using a 5-point Likert scale. These items are related to an individual’s perception of achievements relative to their expectations. A higher value indicates greater life satisfaction.^21^

#### Adherence to the Mediterranean diet

Adherence to the Mediterranean diet will be assessed using the score obtained from the validated 14-item questionnaire of the Prevention of Mediterranean Diet (PREDIMED) study.^22^ A higher score indicates greater adherence to the Mediterranean diet, with a score of ≥9 considered high adherence.^22^

#### Blood pressure

Blood pressure will be measured using an automatic blood pressure monitor (OMRON model HEM-7113, Osaka, Japan), following the general guidelines.^23^ The participant will sit comfortably and quietly for 5 min before the first measurement, with the second measurement taken 2 min later. The final values of systolic blood pressure, diastolic blood pressure and pulse rate were the average of the two measurements. Subjects will be informed to abstain from vigorous exercise for 24 hours, avoid caffeine intake for 4 hours and refrain from tobacco use 30 min before the measurements.

#### Leg muscle strength

The chair stand test will be employed to quantify the leg muscle strength. This test will be carried out following the protocol of previous investigations.^18^

#### Risk of falls

Gait speed is a powerful predictor of fall risk.^24^ Gait speed will be assessed using a 10-metre test.

#### Sagittal spine disposition and pelvic tilt

The sagittal spine disposition and pelvic tilt will be measured using the Spinal Mouse system (Idiag, Fehraltdorf, Switzerland). This device allows the angular measurement of the different spinal curvatures in a non-invasive way. An assessment of the sagittal spine disposition in relaxed standing and sitting will be performed, following the protocol from previous studies.^25^ A positive value implies kyphosis for thoracic and lumbar curvatures and an anteversion for pelvic tilt. In contrast, a negative value implies lordosis for thoracic and lumbar curvatures and a retroversion for pelvic tilt. Each position will be evaluated three times, the final value being the mean of both values.^25^

#### Rating of perceived exertion

The Borg CR-10 RPE scale will be used to measure the perception of exertion among participants.^26^ Participants will be instructed to evaluate their perceived exertion for the entire session and their general perception of exertion for each machine immediately after the session conclusion.

#### Effort and heart rate

The training intensity will be registered by monitoring the HR throughout the sessions. For this purpose, Polar M430 (Polar Electro, Kempele, Finland) wristband HR monitors will be employed. After each session, the average, peak and final HRs will be collected.

#### Training volume

The volume will be systematically registered for each training session. This includes the duration in seconds of the workout, the associated rest intervals and the number of repetitions and sets performed by each participant.

#### Adherence to the exercise programme

In the TG, each participant’s adherence to the exercise programme will be monitored. Adherence will be measured as the percentage of exercise sessions performed and/or the total number of scheduled sessions.

## Patient and public involvement

Patients and/or the public will be involved in this research’s design, performance, reporting or dissemination plans.

## Statistical analysis

The qualitative variables will be summarised in frequency. In contrast, the quantitative variables will be summarised using mean and SD for the TG and CG across the assessment time points. To ensure rigorous statistical evaluation, special attention has been given to controlling the type I (alpha) error and Bonferroni’s correction will be used to achieve p=0.005 for statistical significance. To compare characteristics between and within groups, the principle of intention to treat will be applied, with adjustments made to adhere to the exercise programme. The following tests will be employed to assess baseline characteristic differences between the two groups: Student’s t-test for parametric numerical variables, Mann-Whitney test for non-parametric variables and χ^2^ test for categorical binary variables.

To compare changes within and between the TG and CG across baseline and follow-up assessments, the subsequent tests will be used: for variables exhibiting normal distribution, repeated measures analyses of variance. Given the multiple comparisons involved, post hoc analyses will be conducted using t-tests with Sidak corrections to control the type I error rate; for non-parametric variables, the Friedman test will be followed by the Wilcoxon test, and, to address the multiple comparisons, the Bonferroni correction will be applied.

SPSS V.25.0 statistical software will be used in all the analyses. A p value<0.05 will be used to determine significant differences; however, this will be adjusted appropriately in the presence of multiple comparisons, as detailed above.

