### Ethics approval and dissemination

All participants will be informed about the study procedures and will give their approval through informed consent before inclusion. All data collected during the study will be confidential. All participants receive a final report with their results to know their values at baseline and the end of the study. The trial will be conducted following the Declaration of Helsinki, and the study has been approved by the institutional ethics committee of the Catholic University of Murcia (CE111908).

Based on previous studies, groups larger than 30 were required for the result to reliably characterise precision error or change during clinical monitoring.^9^ A dropout rate of 16% will be assumed based on previous studies,^10^ so a minimum of 35 participants will be included per group. The RStudio V.3.15.0 software will be used to calculate the sample size. The sample size and statistical power were established considering the SD (4.2) in the maximum voluntary isometric contraction (MVIC).^11^ A significance power of 95% (1-β=0.95) and a significance level of 0.05 will be considered. Ultimately, the sample consisted of a minimum of 60 participants per group. This resulted in an assumed error of 1.06.

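### The Bonferroni threshold of 0.005 has no defined family: it matches neither the primary outcome list nor the 0.05 level used to size the trial

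*Protocol article*

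**What the plan says.** The Statistical analysis section sets the threshold: Bonferroni's "correction will be used to achieve p=0.005 for statistical significance". It gives neither the number of tests nor the outcomes covered. It then prescribes repeated-measures analysis of variance with Sidak-corrected post hoc t-tests for normally distributed variables, and Friedman then Wilcoxon tests with Bonferroni for the others. It closes with: "A p value<0.05 will be used to determine significant differences; however, this will be adjusted appropriately in the presence of multiple comparisons, as detailed above".

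The Primary outcomes section has eight headings: maximum muscular strength, handgrip, cardiorespiratory fitness, postural stability, dynamic balance, body composition, functional performance and sarcopenia. Most contain several variables. No heading names its primary variable, and no heading is placed above the others.

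Two measures appear on both sides of the primary/secondary divide:

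- **10 m gait speed.** Under Functional performance (primary): "Functional performance will be measured by 10 m of gait speed, the TUG and the SPPB". Under Risk of falls (secondary): "Gait speed will be assessed using a 10-metre test".
- **Chair stand.** It is part of the SPPB under Functional performance and a strength measure under Sarcopenia, both primary. Under Leg muscle strength (secondary): "The chair stand test will be employed to quantify the leg muscle strength".

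The sample size paragraph, which sits under Ethics approval and dissemination, uses one variable: "The sample size and statistical power were established considering the SD (4.2) in the maximum voluntary isometric contraction (MVIC"). It takes a significance level of 0.05, arrives at 60 per group and reports an assumed error of 1.06. It does not say whether the MVIC is that of the knee or the elbow.

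**The concern.** A Bonferroni level has meaning only relative to a counted family. Here the level is fixed and the family is not, so a reader cannot tell which results would count as confirmatory or what overall error rate the trial accepts. With eight undesignated primary headings, any of several dozen variables could later be presented as the primary result. Two tests could be reported as primary or secondary according to how they turn out.

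MVIC, the only outcome that was sized, was sized at 0.05 but would be judged at a level ten times stricter. The stated sample-size justification therefore does not describe the analysis that the plan sets out.

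**Working it through.** **1. What 0.005 implies.** 0.05/m = 0.005 gives m = 10. Allowing for rounding to three decimals, m = 11 also fits (0.05/11 = 0.0045).

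**2. What the lists contain.** The primary section has eight headings, so one test per heading would give 0.05/8 = 0.00625. Table 2 has twelve outcome rows measured at both baseline and post. Neither list has ten members.

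My count of distinct variables under the primary headings:

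| Heading | Variables | Number |
|---|---|---|
| Maximum strength | knee and elbow × MVIC and rate of force development | 4 |
| Handgrip | peak strength | 1 |
| Cardiorespiratory fitness | 400 m time; maximum, mean, final and 2-min heart rate | 5 |
| Postural stability | 4 centre-of-pressure measures × 3 stances | 12 |
| Dynamic balance | TUG | 1 |
| Body composition | mass, lean %, fat %, bone density at 3 sites, osteoporosis risk, FRAX | 8 |
| Functional performance | 10 m gait, 4 m gait, chair stand, SPPB score (TUG not recounted) | 4 |
| Sarcopenia | appendicular muscle mass, risk class | 2 |
| Total | | 37 |

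The total is 38 if height is included. The argument does not depend on the exact figure, because the postural stability variables alone number 12.

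**3. Error rate at 0.005 per test.** The upper bound is m × 0.005. Under independence the rate is 1 − 0.995^m.

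| m | 0.05/m | Upper bound | If independent |
|---|---|---|---|
| 8 | 0.00625 | 0.040 | 0.039 |
| 10 | 0.005 | 0.050 | 0.049 |
| 37 | 0.00135 | 0.185 | 0.169 |

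**4. The sample size.** Inputs are SD 4.2, n = 60 per group, level 0.05 and stated error 1.06.

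- One-group two-sided 95% half-width: 1.96 × 4.2/√60 = 1.063, which agrees with 1.06. Inverted, (1.96 × 4.2/1.06)² = 60.3.
- One-sided 0.05 precision would need 42.5, which does not fit.
- A two-group comparison detecting 1.06 with 95% power at two-sided 0.05 would need 2 × (1.96 + 1.645)² × 4.2²/1.06², or 409 per group, which does not fit either.

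Of the readings tried, only the one-group precision calculation gives the plan's figure.

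**5. The same calculation at 0.005.** The normal quantile becomes 2.807. The half-width at 60 per group is 2.807 × 4.2/√60 = 1.52. Keeping 1.06 would take (2.807 × 4.2/1.06)² = 123.7, about 124 per group.

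**The case against.** Much can be said for the plan, and some stronger readings go beyond what it states.

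- **An outright clash of 0.05 and 0.005 within the analysis section.** A reader might infer this from "A p value<0.05 will be used to determine significant differences" alone. The sentence goes on to say that the level is adjusted for multiple comparisons as already described. The natural reading is a nominal 0.05 brought down to 0.005, so an error rate based on unadjusted testing at 0.05 would describe a plan that is not stated.
- **Stacked or needless corrections.** Sidak and the post hoc Bonferroni apply to different types of variable, so they do not accumulate on one outcome. The plan compares changes within groups as well as between them, so there are several comparisons per outcome and a post hoc step is not redundant. What is missing is how that step relates to 0.005.
- **Error is simply uncontrolled.** That depends on the family. With one variable per heading the bound is 0.04, and 0.005 would be slightly conservative. The 37 is my count. Many of these variables are correlated or derived from one another, so 18.5% is a ceiling. This stands, but the document designates no variable.
- **A family of about ten might exist.** The abstract can be counted as eight measured domains plus three questionnaires, and 0.05/11 rounds to 0.005. Nothing says this was intended, and that grouping mixes primary with secondary outcomes. The fair statement is that the family is undefined.
- **TUG.** It appears under more than one heading, but all of them are primary, so its status is not in doubt.
- **Detail left to an analysis plan.** Test-level detail may well be. But the article itself fixes the threshold, the outcome hierarchy and the sizing level, and those three do not agree.

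**Conclusion.** The point holds in this form. The threshold of 0.005 corresponds to ten tests (eleven with rounding), while the article lists eight undesignated primary headings containing about 37 variables. If all 37 are tested at 0.005, family-wise error is at most 18.5%, and about 17% under independence. It would be at most 4% if one variable per heading were designated, which the plan does not do. The chair stand and 10 m gait speed have contradictory status.

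The sizing level of 0.05 also differs from the decision level. On the only reading that reproduces the plan's figure, the precision of 1.06 becomes 1.52 at 0.005. These precision figures assume a two-sided normal interval for one group with SD 4.2. They say nothing direct about power for the between-group difference, which the sample size paragraph does not reproduce. The error-rate figures rest on my count of variables and would shift with it, but any reasonable count exceeds ten.

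**What to change.** Make a dated amendment before outcome data are seen by group, and have it say so. This matters because the Introduction describes the trial as ongoing and the Patents section says its results have already been taken into account in machine design. Relaxing a threshold after seeing results by group could not be presented as prespecified. The amendment should:

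1. List each measure once, as primary or secondary, and so settle the chair stand and 10 m gait speed.
2. Designate the primary variable or variables. One option is a single MVIC measure (knee or elbow, chosen now), with the difference between training and control groups in change tested at two-sided 0.05. The other is a fixed number k of primaries, each at 0.05/k or by Holm. The choice between them is partly a design preference.
3. Replace 0.005 with the level that follows, and restate the precision or power of 60 per group at that level, without enrolling more participants.
4. Report all other measures as secondary, with estimates and 95% confidence intervals.
5. State that the Sidak and Bonferroni post hoc steps apply only to within-group and single-time-point comparisons, not to the primary between-group contrast.

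The change is to the text only. The downside is that some measures lose confirmatory status, and if several primaries are kept the stated precision will look less favourable than 1.06.

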## Materials and methods

### Study design and setting

This protocol describes an 8-week two-armed parallel single-blind randomised controlled trial with blinded examiners (NCT04958499). This study is designed considering the recommendations of Consolidated Standards of Reporting Trials 7 and Standard Protocol Items: Recommendations for Interventional Trials statements.^8^

Participants will be evenly and randomly divided between the training group (TG) and the CG. The overall study design is summarised in figure 1. The choice of this design is related to the main objective and facilitating the interpretation of the data with intragroup and intergroup.

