### Inclusion and exclusion procedures

To be included in the study, participants will have to meet the following criteria: will be male or female, aged 50 years or older, being physically independent, not having any pathology incompatible with the study, not having participated in a structured exercise programme for at least 1 year and signing the informed consent form. The exclusion criteria will be self-reported substance abuse or dependence disorder (alcohol, non-prescribed medications, etc), being under medical prescription for taking medications that could influence physical performance, suffering from any pathology contraindicated for the exercise programme or requiring specialised medical attention (infectious, renal, pulmonary, coronary diseases, etc), having low adherence during the programme or performing physical exercise outside the study. During the pre-test phase, health personnel will perform an ECG on each participant to corroborate their cardiac health just after signing the informed consent and before the assessment tests.

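### The repeated-measures ANOVA uses baseline only through change scores: a baseline-adjusted TG–CG difference would be more precise at no cost and would fix the deciding contrast

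*Protocol article*

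**What the plan says.** The hypothesis at the end of the Introduction is between-group: the training group (TG) is expected to improve relative to the control group (CG).

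The Statistical analysis section states its aim as "To compare changes within and between the TG and CG across baseline and follow-up assessments". The model is, "for variables exhibiting normal distribution, repeated measures analyses of variance", after which "post hoc analyses will be conducted using t-tests with Sidak corrections". For the remaining numerical outcomes, "the Friedman test will be followed by the Wilcoxon test". Bonferroni's correction sets the significance threshold at 0.005.

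The section does not say which term of the ANOVA tests the hypothesis, and baseline is not used as a covariate. Study design and setting gives as one reason for the design "facilitating the interpretation of the data with intragroup and intergroup", so both kinds of reading are intended and neither is ranked above the other.

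Table 2 schedules the continuous health outcomes once at baseline and once after the intervention. Randomisation and allocation places baseline measurement before assignment.

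**The concern.** With two time points, the between-group information in a repeated-measures ANOVA lies in the group-by-time interaction, which is a comparison of mean change. A change score subtracts the whole baseline value, although regression to the mean implies that only a fraction of it (the correlation, if the SDs are equal) should be subtracted. The estimate is unbiased under randomisation but carries avoidable noise, and this applies to every continuous outcome. The loss matters more at a threshold of 0.005 than at 0.05.

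The second part is which contrast decides. The ANOVA yields several tests, and the plan covers changes within as well as between arms without naming one estimate as the answer to the hypothesis. This leaves room for a conclusion drawn from a significant change in the TG alone, which is not a comparison with the CG.

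**Working it through.** **Inputs**
- 60 per group and SD 4.2 for MVIC: sample-size paragraph, placed under Ethics approval and dissemination.
- Threshold 0.005: Statistical analysis. Two-sided testing is assumed, so z = 2.807.
- Baseline–post correlation rho: not given; 0.5, 0.7 and 0.9 are assumed.
- Effect of 0.5 SD: assumed, for illustration.

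**The plan's own figure.** The sample-size paragraph reports an error of 1.06. It reproduces as the half-width of a 95% interval for one mean: 1.96 × 4.2/√60 = 1.063. It is not a between-group target difference, so the plan gives no planned effect against which to judge the model. Hence the assumed 0.5 SD.

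**Variance.** With the same SD (s) at both visits and correlation rho, the per-person variances are:
- change score (group-by-time test): 2(1 − rho)s²
- baseline-adjusted post value (ANCOVA): (1 − rho²)s² = (1 − rho)(1 + rho)s²
- ratio, ANCOVA to change: (1 + rho)/2

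| rho | ratio | extra participants the change score needs (1/ratio − 1) |
|---|---|---|
| 0.5 | 0.75 | 33% |
| 0.7 | 0.85 | 18% |
| 0.9 | 0.95 | 5% |

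**Power at 0.005, 0.5 SD, 60 per arm** (normal approximation; z = 0.5/√(2v/60), where v is the per-person variance in units of s²; power = Φ(z − 2.807)):
- rho 0.5: ANCOVA v = 0.75, z = 3.16, power 64%; change v = 1.00, z = 2.74, power 47%.
- rho 0.7: ANCOVA v = 0.51, z = 3.83, power 85%; change v = 0.60, z = 3.54, power 77%.
- rho 0.9: ANCOVA v = 0.19, z = 6.28; change v = 0.20, z = 6.12; both above 99%.

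At a threshold of 0.05 and rho 0.7 the gap is smaller: 97% against 94%.

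**Why within-arm p-values should not decide.** Suppose both arms truly change by the same 0.5 MVIC units (SD 4.2, 60 per arm), so there is no treatment effect. The standard error of an arm's mean change is 4.2 × √(2(1 − rho)/60). The chance p that a given arm is significant at 0.05 is 0.222 at rho 0.7 and 0.541 at rho 0.9. The chance that exactly one arm is significant is 2p(1 − p) = 0.35 and 0.50. At 0.005 it is 0.10 and 0.35.

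**Dropout.** Both methods were simulated with no true effect, SD 4.2, 60 per arm and an assumed 16% loss, leaving about 50 per arm in either analysis. At rho 0.7:
- loss completely at random: no bias in either method;
- loss depending on arm and baseline: bias −0.28 for the ANOVA, 0.00 for ANCOVA;
- loss in the TG depending on the unobserved outcome: bias 0.34 in both.

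The size of these biases depends on the dropout pattern assumed. The pattern of the results is the point: adjustment helps in the second case and not in the third.

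**The case against.** The strongest reply is that nothing planned here is invalid. The article says that changes will be compared between groups as well as within them. In a two-arm, two-visit ANOVA that comparison is the interaction, which is unbiased under randomisation. For repeatable strength tests rho may well be 0.7 to 0.9, where the variance saving is 15% down to 5%. A separate analysis plan could also name the deciding contrast. All of this stands. It makes the point one of efficiency and clarity. It does not remove it, because the article itself fixes the model.

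Three stronger readings are tempting but unsupported.
- A reader might infer that the group main effect, which averages baseline with follow-up and so halves the treatment effect, will be taken as the result. Nothing says so, and the wording about changes points to the interaction.
- A reader might infer that the Sidak t-tests are within-arm only. The text does not restrict them.
- A reader might infer that the analysis breaks intention to treat because of dropout, and that adjustment would repair it. The article does not say how missing post values are handled, and an article may leave this to the full plan. The passage "A dropout rate of 16% will be assumed based on previous studies" belongs to the 35-per-group figure, not to the 60. ANCOVA also needs a post value, and in a mixed model with two visits a person with baseline only adds almost nothing about the treatment effect.

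The tension over intention to treat that the text does show lies elsewhere: "the principle of intention to treat will be applied, with adjustments made to adhere to the exercise programme", alongside an exclusion criterion of "having low adherence during the programme or performing physical exercise outside the study". Those two statements need reconciling whichever model is used.

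**Conclusion.** The point holds as a free improvement, not as an error that invalidates the analysis. The planned group-by-time test is a sound but less precise comparison, and the plan does not name the one TG–CG estimate that answers its hypothesis.

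The gain depends on rho, which the article does not give: material at 0.5, moderate at 0.7, negligible for power at 0.9 in the example used. The figures assume equal SDs at the two visits, a two-sided test, complete data on 60 per arm and an effect of 0.5 SD. Apart from one degree of freedom, adjustment is not expected to cost precision in this randomised design. Its benefit under dropout is limited to loss that depends on baseline and arm.

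**What to change.** State in the Statistical analysis section that, for each continuous outcome, the main analysis is the TG–CG difference in the post-intervention value adjusted for the baseline value of that outcome, reported with its 95% confidence interval. ANCOVA serves, as does an equivalent mixed model with a common baseline mean. State that efficacy conclusions rest on this difference and that within-arm changes are descriptive.

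Apply the same principle to the outcomes now sent to Friedman and Wilcoxon tests. As ordinarily used in that sequence, these are within-subject tests and give no between-group comparison of change.

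Do not present the adjustment as delivering intention to treat. That needs its own statement of who is analysed and how missing post values are handled.

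The cost is a change of analysis wording. Baseline values are already scheduled before randomisation, and no extra data or participants are needed.
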